## Abstract

**Background:** Symptoms of insomnia are common in new mothers and have been associated with a range of negative maternal and child outcomes. Despite this, interventions to improve maternal postpartum sleep remain scarce. Cognitive Behavioural Therapy (CBT) and Light Dark Therapy (LDT) represent two promising interventions for insomnia symptoms and associated daytime consequences such as fatigue. This randomised controlled trial examines whether CBT and LDT improve maternal insomnia symptoms as the primary outcome and maternal sleep disturbance, mood, fatigue, and sleepiness as secondary outcomes. This protocol paper outlines the development, design, and implementation of the trial.

**Methods:** Participants are an Australian community-sample of 90 first-time mothers who are 4–12 months postpartum with self-reported symptoms of insomnia (Insomnia Severity Index scores ≥ 8). Exclusion criteria include current severe sleep/psychiatric disorders, unsettled infant sleep behaviour, sleep-affecting medication use, and photosensitivity. Eligible women are randomised into a CBT (strategies targeting sleep, worries, fatigue, and relaxation), LDT, or a treatment-as-usual control condition. Interventions are therapist-assisted and personalised through two telephone calls and include a series of automated intervention emails delivered over 6 weeks. Primary and secondary outcomes are assessed at four time points: baseline, intervention mid-point, post-intervention, and 1-month post-intervention.

**Discussion:** If found effective, these interventions could represent efficacious, safe, and inexpensive treatments for improving postpartum insomnia and mitigate its negative impact on maternal well-being. Interventions tested are highly scalable and can be integrated into postpartum care and made available to the broader community.

**ANZCTR trial registration:** Accessible at: https://anzctr.org.au/Trial/Registration/TrialReview.aspx?ACTRN=12618000842268.

## Introduction

Following childbirth, women experience inconsistent sleep-wake times, overnight awakenings and daytime napping to compensate for poor nighttime sleep (1–6). While some aspects of sleep (e.g., sleep duration) may eventually improve over time, others (e.g., sleep efficiency) continue to be compromised beyond the initial postpartum months (2, 3) with a significant proportion (41%) of women reporting significant insomnia symptoms at 2 years postpartum (7).

Maternal insomnia symptoms have been associated with a range of negative outcomes including mood disturbance (8–11), fatigue (12, 13), and family dysfunction (14). While there has been some progress in infant sleep interventions (15, 16), evidence-based interventions to aid maternal sleep during the postpartum period, despite being imperative, remain notably limited (17).

Postpartum insomnia symptoms may develop via different mechanisms. From cognitive behavioural perspectives, disturbed sleep experienced during pregnancy and early postpartum may precipitate unhelpful sleep behaviours (e.g., spending excessive time in bed) and cognitions (e.g., worries about consequence of poor sleep), which may perpetuate symptoms of insomnia. Cognitive Behavioural Therapy (CBT) for insomnia is a non-pharmacological intervention that targets underlying cognitive and behavioural factors that perpetuate insomnia through various recommendations such as stimulus control, sleep restriction, cognitive strategies, relaxation training, and sleep hygiene (18); it is shown to be a safe treatment option (19) and highly effective for reducing insomnia in diverse populations (20, 21), including in pregnant women with insomnia (22, 23). Even while external factors (e.g., infant awakenings) disrupt sleep, CBT remains effective in that it increases sleep drive, reduces conditioned arousal and alters maladaptive cognitions and behaviours underlying insomnia (18). A recent randomised controlled trial (RCT) of CBT for insomnia during pregnancy demonstrated significant improvements in insomnia symptoms for women in the intervention condition compared to those in the control (22).

A second potential mechanism of postpartum insomnia is circadian rhythm disturbance. Dampened circadian amplitude and phase delays have been reported during perinatal periods (11, 24, 25). It is possible that altered sleep-wake timing (3, 26) and low levels of light exposure (27) during postpartum periods may underlie these changes. Circadian disruption has been linked to symptoms of insomnia (28) and mood disturbance (29–32). Light therapy involves appropriately-timed light exposure to realign the circadian clock with externally required sleep/wake timing (33) and/or to reduce sleepiness through its direct alerting effects (34). There may also be provision of strategies to reduce light exposure at night (i.e., Dark Therapy), such as through the use of light-blocking glasses (33, 35). Light therapy has been shown to be safe (33) and an effective intervention for improving sleep disturbance (36), fatigue (37), and mood (38), including depression in both general (39) and perinatal (40) populations. The benefits of light therapy for improving postpartum insomnia symptoms and associated daytime consequences such as postpartum fatigue, however, remains to be elucidated.

The aim of the current study is to simultaneously evaluate the efficacy of CBT and Light Dark Therapy (LDT), two distinctive interventions targeting two different potential mechanisms (i.e., cognitive-behavioural and circadian) of postpartum insomnia to accelerate intervention development. It is hypothesised that compared to a treatment-as-usual (TAU) control condition, women who receive either intervention will demonstrate significantly greater improvements in maternal insomnia symptoms as the primary outcome, and maternal sleep disturbance, fatigue, sleepiness, and symptoms of depression and anxiety as secondary outcomes. This comparator was selected as an ideal control to assess efficacy of interventions compared to existing clinical practices of routine perinatal care (41).

## Methods

### Design

This is a parallel-group, randomised controlled efficacy trial, consisting of two intervention conditions (CBT and LDT) and one TAU control condition, randomised in a 1:1:1 ratio. Outcomes are assessed at baseline (Week 0; T0), intervention mid-point (Week 3; T2), post-intervention (Week 6; T3), and 1-month follow-up (Week 10; T4). This protocol follows SPIRIT-PRO (42) and TIDieR (43) guidelines (see Supplementary Material). Please see Figure 1 for details.

**Figure 1 F1:**
[figure not shown]
Flowchart of trial procedures.

### Participants

Inclusion criteria are: (a) nulliparous women (i.e., first-time mothers with no older children) 4–12 months postpartum; (b) age ≥18 years; (c) reports symptoms of insomnia, operationalised as scoring ≥8 (subthreshold insomnia) on the Insomnia Severity Index [ISI; (44)]; (d) singleton pregnancy; (e) ability to read and write in English; (f) regular access to telephone, email and the internet. Nulliparous women were chosen given the higher risk of poorer sleep compared to multipara (2, 45, 46).

Exclusion criteria are: (a) current pregnancy; (b) night shift work; (c) current severe or untreated sleep disorders (e.g., narcolepsy, sleep apnea, restless legs syndrome, circadian rhythm disorders); (d) take medications or have medical conditions that directly affect sleep (e.g., sleep medication, antidepressants); (e) report current severe psychopathology (e.g., bipolar disorder, post-traumatic stress disorder) or are at high risk of harm to self/others; (f) have infants with medical conditions that affect sleep; (g) suffer from epilepsy; (h) report photosensitivity or have been recommended by health professional to avoid bright light; (i) report current unsettled infant sleep behaviour, operationalised as infant waking on average >3 times per night and requiring parental assistance to reinitiate sleep; this final exclusion criterion was established as this trial focuses on the management of maternal insomnia symptoms rather than sleep deprivation primarily due to infant care. Participants are permitted to receive ongoing usual care for physical and/or mental health conditions.

### Procedure

#### Recruitment

The study is referred to as the Postpartum Sleep Study for Mothers and a mixture of community and online recruitment are used. Facebook groups for parents within Australia are approached to post a “call for participants” containing information about the trial alongside a link to the online explanatory statement. Various maternal and child health centres within metropolitan Melbourne are contacted to assist with distribution of project information. Relevant Australian organisations and media outlets are contacted with details of the project and asked encouraged to share information with consumers.

#### Informed Consent

The explanatory statement includes comprehensive details of the project such as information regarding interventions, assessments, research procedure, potential risks, reimbursement, confidentiality, and freedom to withdraw participation. After reading the online explanatory statement, participants proceed to complete brief screening questions before providing informed consent (see Supplementary Material). Women <4 months postpartum may still provide their consent and are contacted once they have reached the appropriate time frame for inclusion. Women who do not fulfil initial eligibility are directed to a list of further support services.

#### Telephone Interview and Screening

Baseline questionnaire responses are reviewed and respondents who do not yet met exclusion criteria are contacted to undertake a telephone screening interview to assess further eligibility. The telephone interview covers: the Duke Structured Interview for Sleep Disorders [DSISD; (47)], sleep/wake habits, medication use, engagement in psychotherapy or sleep treatments, and a risk assessment. Women ineligible upon initial screening are provided with a list of suitable support services, discussed with them via telephone and reiterated in a follow-up email.

##### Risk Assessment

A risk assessment is undertaken during the initial telephone interview, as well as during mid-point and post-intervention telephone calls (discussed further). It assesses suicidal/homicidal ideation, plan, history of injurious behaviour, and engagement with mental health care. During the initial interview, women deemed to be at high risk, operationalised as current suicidal/homicidal ideation with plan and/or history of harm, are excluded from the study and referred to relevant services for clinical care. Women at medium risk, operationalised as experiencing current depression with ideation to harm self/others but have no plan, are included if no exclusion criteria have been met; these women are encouraged to seek professional help for their mental health via general practitioner or psychologist, and will also be provided with details of relevant mental health services. Women at low risk are included if no exclusion criteria are met.

Initial and mid-point telephone calls are carried out by a provisional psychologist undertaking doctoral training in clinical psychology (SV) who consults a clinical psychologist (BB) when any risk issues arise to decide on appropriate action. Risk assessments in the post-intervention telephone call are undertaken by research assistants who received training by a provisional (SV) and clinical psychologist (BB). Research assistants contact the provisional psychologist (SV) if any risk issues arise, who consults the clinical psychologist (BB) to decide on appropriate action.

#### Randomisation and Blinding

Eligible participants are randomised using a complete randomisation scheme generated in advance. Specifically, block sizes of variable size (3, 6, 9) are used. Random seeds are generated to assure allocation concealment and pre-guessing of the allocation sequence at the end of each block. Randomisation are stratified by baseline ISI (≤ 14 and >14) and infant age (<8 months and ≥8 months). As noted on trial registration, this protocol commenced as a four-arm trial with the fourth arm receiving both CBT and LDT. Due to significant and unexpected changes in the first author's personal circumstances during the early phase of this trial, this fourth arm was removed after 31 participants were randomised (9 to the removed condition) to ensure timely trial completion. Randomisation used during this initial phase was identical to subsequent 3-arm randomisation described above, except the randomisation scheme had block sizes of 4 or 8.

The randomisation scheme is generated in R (48) and is set up in REDCap by a member of the research staff who is not involved in recruitment or delivery of intervention and not a principal investigators. To randomise a participant, an authorised research staff member logs into REDCap, enters eligibility and participant stratification data before receiving group allocation. Participants are not blinded but are asked to withhold group allocation from research assistants during the post-intervention telephone call.

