#### Other Factors

Demographic, medical conditions, and obstetric information are collected using self-report at baseline (T1) and changes are monitored at T3 and T4 (e.g., infant-feeding method, medical conditions of mother/infant, engagement in therapy, medication use).Postnatal Sleep Questions include self-reported maternal sleep behaviours over the past week (e.g., sleep duration, onset latency, wake after sleep onset, daytime naps adapted from the Consensus Sleep Diary (63).Self-reported maternal sleep history (i.e., pre-pregnancy sleep) are assessed using adapted versions of the PROMIS-SD-SF and Postnatal Sleep Questions.Maternal mental health, measured with the Cross-Cutting Symptoms Level 1 (64).Mother-infant attachment quality, assessed using the Mother to Infant Bonding Scale (65).Relationship satisfaction with the partner, measured using the brief Dyadic Adjustment Scale – 4 (66).The following are assessed and examined as potential covariates: infant sleep [Brief Infant Sleep Questionnaire; (67)]; perceived stress [Perceived Stress Scale; (68)]; social support measured using the PROMIS Instrumental Support – Short Form – 4a and PROMIS Emotional Support – Short Form – 4a (69); questions on the partner's sleep behaviour and overnight assistance with infant care are also included.Feasibility and acceptability are assessed implicitly via recruitment and dropout rates, and explicitly via the Client Satisfaction Questionnaire (70) and qualitative feedback from participants.Due to ongoing data collection during the COVID-19 pandemic, questions related to personal experiences with COVID-19 and potential impact on participation are asked to all participants who completed the project after mid-February 2020 (shortly before the outbreak was declared a national pandemic in Australia). This is intended to assist with interpreting findings from this trial following completion.

The following constructs will also be measured and explored as predictors or mediators of treatment responses:

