Primary and secondary outcomes will be examined using latent growth models. Piecewise models will be used to allow different rates of change: from baseline (T0), through mid-point (T2), to immediate post-intervention (T3) called Slope 1, and from immediate post-intervention (T3) to one-month follow-up (T4) called Slope 2. Loadings for Slope 1 will be 0 for T0 (fixed), freely estimated for T2, 1 for T3 (fixed), and 1 for T4 (fixed). Loadings for Slope 2 will be fixed at 0 for T0, T2, and T3 and fixed at 1 for T4. This model is saturated for the outcome means at each timepoint to ensure that change over time is accurately modeled. The primary trial endpoint for all outcomes is Slope 1, which captures change from baseline to post-intervention. Slope 2 captures maintenance of treatment results over the one-month follow-up and is an exploratory endpoint. The residual variance will be constrained to be equal across time (homogenous) and independent (i.e., an independent, homogenous residual structure). Intercepts of manifest variables for the outcomes will be constrained to 0 to allow estimation of the latent random intercept mean. The intercept and Slope 1 variances and covariances will be freely estimated. The variance of Slope 2 and its covariance with the intercept and Slope 1 will be freely estimated if possible, but given it comprises only two timepoints, if there are convergence or estimation problems, the variance of Slope 2 will be constrained to 0. The two stratification factors, ISI (≤ 14 and >14) and infant age (<8 and ≥8 months) will form four grouping conditions: Early Postpartum Low ISI, Late Postpartum Low ISI, Early Postpartum High ISI, and Late Postpartum High ISI. Dummy codes will be created for each, with Early Postpartum Low ISI as the reference group. These dummy codes will be included as covariates to adjust for effect on the random intercept (79, 80).

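### Women were randomised from two successive lists, but the growth model adjusts only for the ISI-by-age strata: a small precision loss in the three-arm comparison, and bias only if the nine combined-arm women are analysed

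*Protocol article*

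**What the plan says.** Randomisation and Blinding describes two schemes used one after the other. At the start, "this protocol commenced as a four-arm trial with the fourth arm receiving both CBT and LDT". Then "this fourth arm was removed after 31 participants were randomised (9 to the removed condition) to ensure timely trial completion". The initial scheme matched the later one, including stratification by baseline ISI and infant age, "except the randomisation scheme had block sizes of 4 or 8". In the current three-arm scheme, "block sizes of variable size (3, 6, 9) are used". The Design section gives the present trial as two interventions and "one TAU control condition, randomised in a 1:1:1 ratio".

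Statistical Analysis forms four groups from the two stratification factors and states: "These dummy codes will be included as covariates to adjust for effect on the random intercept". The primary endpoint is Slope 1, the change from baseline to post-intervention. Treatment enters as two indicators, one for CBT present or absent and one for LDT present or absent. All analyses are by intention to treat. The one named sensitivity covariate is sleep treatment received outside the study. No term for list, phase or calendar time appears there or among the potential covariates under Other Factors. The article does not say whether the nine combined-arm women count towards the 90 or enter the analysis.

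**The concern.** The plan follows the sound principle of adjusting for the groups within which allocation was made, but it leaves one of them out. Blocks were filled within list as well as within stratum, so the list is a randomisation stratum in all but name. It also separates early from later recruits. If ISI change differs between those periods, the planned stratum terms do not absorb the difference: they act on the intercept, and the primary endpoint is a slope.

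What is at stake depends on who is analysed. With the three retained arms only, an unmodelled phase difference goes into residual variation. With the nine combined-arm women included, treatment presence is related to phase, because all nine belong to the four-arm period and carry both indicators. A phase difference would then be read partly as a treatment effect.

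**Working it through.** The article gives no figure for this point. Its 82% power depends on a within-person correlation and a test that it does not state, and nothing below rests on it.

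**Counts (Randomisation and Blinding).** 31 − 9 = 22 women from the four-arm list are in the retained arms, about 22/3 = 7.3 per arm. Every block in that list held 4 or 8. Since 31 is not a multiple of 4, at least one block was incomplete when the list was stopped.

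**Case A: CBT, LDT and TAU only.** The expected share of each arm is 1/3 under both lists, so phase and treatment are unrelated in expectation and no bias is expected. What remains is variance. Assume that the 90 excludes the nine (p = 22/90 = 0.244) and that the SD of ISI change is 4.5; neither is stated in the article. The share of variance due to a phase difference of d points is p(1 − p)d²/4.5², with p(1 − p) = 0.1847 and 4.5² = 20.25:

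| d (assumed) | Share of variance |
|---|---|
| 1 | 0.9% |
| 2 | 3.6% |
| 3 | 8.2% |

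**Case B: the nine women kept under presence/absence coding.** CBT is present in (7.33 + 9)/31 = 53% of four-arm-list women and in 33% of later women; the same holds for LDT. The bias in each treatment effect is the phase difference times the coefficient from regressing phase on the two indicators.

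- Take cells of 30 TAU, 30 CBT, 30 LDT and 9 both (N = 99). The four-arm-list share is 0.244 in the single-arm and TAU cells and 1 in the combined cell.
- By symmetry, work with s = CBT + LDT. Mean s = 78/99 = 0.788. Variance = 96/99 − 0.788² = 0.349.
- Covariance of s with combined-arm membership = 18/99 − (9/99)(0.788) = 0.110.
- Coefficient = (0.110/0.349) × (1 − 0.244) = 0.239.
- If the nine are inside the 90 (cells 27, 27, 27, 9), it is (0.12/0.36) × (1 − 22/81) = 0.243.

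So about 0.24 of the phase difference enters each effect: 0.24, 0.48 or 0.72 ISI points for assumed differences of 1, 2 or 3 points.

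**Simulation.** There were 6000 replicates per scenario: stratified four-arm blocks of 4 or 8 for 31 women, then three-arm blocks of 3, 6 or 9 for 68 or 59 more. The analysis was least squares on a change-type outcome with SD 1, a stand-in for the latent growth model. Phase effects (0 to 0.8 SD) and the stratum mix (30/30/20/20) are assumed. Monte Carlo error on rejection rates is about 0.003.

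| Analysis set | Phase effect (SD) | Bias, no phase term (SD) | Type I error, no phase term | Type I error, with phase term |
|---|---|---|---|---|
| Three arms | 0 to 0.8 | at most 0.01 | 0.040–0.051 | 0.047–0.057 |
| Nine kept | 0.3 | 0.06–0.07 | 0.054–0.061 | 0.051–0.054 |
| Nine kept | 0.5 | 0.10–0.11 | 0.067–0.072 | 0.048–0.051 |
| Nine kept | 0.8 | 0.17 | 0.095 | 0.049 |

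With the phase term, bias is about zero throughout. The simulated biases are close to 0.21 of the phase effect rather than 0.24 because the simulation puts on average 31/4 = 7.75 women in the combined arm, not the nine observed.

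In the three-arm set, for a treatment effect of 0.6 SD and a phase effect of 0.5 SD, power is 0.62 without the term and 0.64 with it. These powers compare two models. They do not re-estimate the planned power.

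**The case against.** The strongest reply is that the article describes a trial of 90 women in three arms at 1:1:1 and calls the fourth arm removed. For that trial the omission does no harm to validity, and two points of power under an assumed phase effect is fine tuning. This stands in full for Case A. A reader might infer that phase confounds the CBT, LDT and TAU comparison; the equal ratio under both lists rules that out in expectation.

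A second reply is that the material harm arises only if the nine women are analysed, which is a separate undecided matter. That is partly right. The article does not say that they will be analysed. But intention-to-treat wording together with presence/absence coding would admit them, and no sentence excludes them, so the consequence for the covariate set belongs here.

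A third reply is that a term on the slopes goes beyond what the plan does for its declared strata, in a model where estimation trouble with Slope 2 is already foreseen. That is fair, and it argues for restraint on Slope 2. It does not argue against a term on Slope 1, because an intercept-only term would not remove a phase difference in change.

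Three further inferences go past the text:

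- **The list as a pandemic marker.** The article notes, "Due to ongoing data collection during the COVID-19 pandemic", that extra questions were added. It does not date the change of list beyond placing it early in the trial. With about 90 − 22 = 68 women on the second list, that list plausibly mixes women from before and during the pandemic.
- **Broken blocks in several strata.** The counts prove only one.
- **A stored list variable.** The article says the scheme was set up in REDCap, not that the list is held as a field. It should be recoverable from the allocation records.

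**Conclusion.** The point holds as an omitted randomisation factor whose weight depends on the analysis set. For CBT, LDT and TAU alone there is no expected bias. If change differs by phase, tests are slightly conservative and a little precision is lost. If the nine combined-arm women are kept under the presence/absence coding, about 0.24 of any phase difference in ISI change enters both treatment effects. In the simulation, type I error then rises to about 0.07 at a phase effect of 0.5 SD and 0.095 at 0.8 SD.

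The size of any phase difference and the SD of 4.5 are assumptions. The article offers no evidence that such a difference exists. An analysis plan not shown here might add the term, but the article names its covariates explicitly and phase is not among them.

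**What to change.** Add a randomisation-phase indicator (four-arm list or three-arm list), derived from the allocation records, as a covariate on the intercept and on Slope 1 alongside the stratum terms. Extend it to the exploratory Slope 2 only if the model estimates stably.

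State whether the nine CBT plus LDT women enter the analysis. If they do, the phase term on Slope 1 is required. If they do not, it is a worthwhile precision adjustment. Data Storage and Management places analysis after all data are collected, so both statements can still be fixed in advance.

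The cost is two extra parameters, or three with Slope 2, in a model of about 90 women. Where there is no phase effect, simulated power at 0.6 SD changes from 0.646 to 0.644 in the three-arm set, and from 0.773 to 0.753 if the nine are kept.
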